| **17. Research funding and conflicts of interest**  **17.4. Conflict of interest**  The chief principal investigator receives a personal income of > 1 million yen per year from Bayer Yakuhin, Ltd.; however, this will not result in any undue influence of the company on the results of this study. Moreover, a principal investigator receives a personal income of > 1 million yen per year, and a co-investigator receives a personal income of > 2.5 million yen per year, from Bayer Yakuhin Co., Ltd.; however, this will not result in any undue influence of the company on the results of this study. | **17. Research funding and conflicts of interest**  **17.4. Conflict of interest**  A co-investigator receives a personal income of > 1 million yen per year from Bayer Yakuhin Ltd.; however, this will not result in any undue influence of the company on the results of this study. | Correction based on the latest conflict of interest status |

**Purpose**

1. The purpose of this statistical analysis plan is to report the methods for statistical analysis for the study protocol in the "Effects of FInerenone on Vascular Stiffness and Cardiorenal Biomarkers in Chronic Kidney Disease with Type 2 Diabetes (FIVE-STAR)" study (henceforth referred to as "this study").

## **Changes from the research plan**

None

## **Abbreviations**

| Abbreviation | Definition (English) | Definition (Japanese) |
| --- | --- | --- |
| ACE | Angiotensin-converting enzyme | Angiotensin-converting enzyme |
| AI | Augmentation index | Amplification factor / increased pressure factor |
| ARB | Angiotensin II receptor blocker | Angiotensin receptor blocker |
| ARNI | Angiotensin receptor-neprilysin inhibitors | Angiotensin receptor neprilysin inhibitors |
| BMI | Body mass index | Body mass index |
| CAVI | Cardio-ankle vascular index | Cardio-ankle vascular index |
| Child-Pugh | - | An index showing the degree of liver damage |
| CKD | Chronic kidney disease | Chronic kidney disease |
| ClinicalTrials.gov | - | US Clinical Trials Registry Database |
| CRB | Certified review board | Certified clinical research review board |
| CRF | Case report form | Case report form |
| DPP-4 | Dipeptidyl peptidase 4 | Dipeptidyl peptidase 4 |
| E | - | Early diastolic flow velocity waveform of mitral valve orifice |
| E/e’ | - | Early diastolic left ventricular inflow mitral annular velocity ratio |
| EDC | Electric data capture | Electronic data capture |
| eEV | Estimated extracellular volume | Estimated extracellular fluid volume |
| eGFR | Estimated glomerular filtration rate | Estimated glomerular filtration rate |
| ESA | Erythropoiesis-stimulating agent | Erythropoiesis-stimulating agent |
| FAS | Full analysis set | Full analysis set |
| GLP-1 | Glucagon-like peptide-1 | Glucagon-like peptide-1 |
| HbA1c | Hemoglobin A1c | Hemoglobin A1c |
| HFrEF | Heart failure with reduced ejection fraction | Heart failure with reduced ejection fraction |
| HIF-PH | Hypoxia-inducible factor prolyl-hydroxylase inhibitor | Hypoxia-inducible factor prolyl hydroxylase |
| IgA | Immunoglobulin A | Immunoglobulin A |
| jRCT | Japan Registry of Clinical Trials | Japan Registry of Clinical Trials |
| LAD | Left atrial dimension | Left atrial dimension |
| LAVI | Left atrial volume index | Left atrial volume index |
| L-FABP | Liver-type fatty acid-binding protein | L-type fatty acid binding protein |
| LLT | Lowest level term | Lowest level term |
| LVEF | Left ventricular ejection fraction | Left ventricular ejection fraction |
| LVMI | Left ventricular mass index | Left ventricular mass index |
| MedDRA/J | Medical Dictionary for Regulatory Activities/Japanese version | Medical Dictionary for Regulatory Activities/Japanese version |
| MMRM | Mixed-effects models for repeated measures | Mixed-effects models for repeated measures |
| MRA | Mineralocorticoid receptor antagonist | Mineralocorticoid receptor antagonists |
| NAG | N-acetyl-β-d-glucosaminidase | N-acetylglucosaminidase |
| NGAL | Neutrophil gelatinase-associated lipocalin | Neutrophil gelatinase-associated lipocalin |
| NYHA | New York Heart Association | New York Heart Association |
| PPS | Per-protocol set | Per-protocol set |
| PT | Preferred term | Preferred term |
| RA | Renin-angiotensin | Renin-angiotensin |
| Septal e’, lateral e’ | - | Septal and lateral mitral annulus movement speed |
| SGLT2 | Sodium glucose cotransporter 2 | Sodium-glucose cotransporter 2 |
| SOC | System organ class | System organ class |
| SS | Safety set | Safety set |
| TEAE | Treatment-emergent adverse event | Adverse events occurring after baseline |
| UACR | Urine albumin-to-creatinine ratio | Urinary albumin/creatinine ratio |
| α1-MG | α1-microglobulin | α1-microglobulin |
| β2-MG | β2-microglobulin | β2-microglobulin |

--: Indicates no appropriate term.

# **Research summary**

## **Research objective**

To evaluate the effects of finerenone on vascular stiffness using cardio-ankle vascular index (CAVI) and cardiorenal biomarkers in patients with chronic kidney disease and type 2 diabetes.

## **Study drug**

Finerenone (brand name: Kerendia® tablets 10 mg/20 mg)

## **Study design**

Investigator-initiated, multicenter, prospective, parallel-group, placebo-controlled, double-blind, randomized controlled trial

## **Study participants**

Patients with chronic kidney disease and type 2 diabetes

## **Target number of cases**

100 cases (Finerenone group, 50 cases; Placebo group, 50 cases)

## **Research methodology**

After verifying the eligibility of patients providing written consent, patients meeting the inclusion criteria will be enrolled in the study. Patients will be randomized (allocated) to the finerenone or placebo groups and will undergo double-blind administration, observation, and prescribed tests at baseline (before the study drug administration) and 4, 12, and 24 weeks after study drug administration. In principle, baseline tests will be conducted within 60 days of obtaining consent, and study drug administration will be initiated the following day.

# **Analysis** **population**

## **Randomized set**

All participants who were allocated to either treatment group following study registration.

## **Efficacy analysis set**

Regarding efficacy, the full analysis set (FAS) will be the primary analysis set, and a supplementary analysis will be conducted with the per-protocol set (PPS) for sensitivity analysis.

### **Full analysis set (FAS)**

In accordance with the intention-to-treat principle, the FAS excluding the following patients from the randomized set will be used for efficacy analysis:

- Patients who withdrew consent after enrollment
- Patients who were identified as ineligible after enrollment
- Patients who never received protocol treatment after allocation
- Patients with no data on efficacy after protocol treatment initiation

### **Per-protocol set (PPS)**

Among the FAS, the patients without any significant deviations from the study plan will be included in the PPS and will be used for supplementary efficacy analysis.

The data center will evaluate deviations from the study plan as cases accumulate. Furthermore, before the study data set is finalized, a case review meeting will be conducted with the principal investigator, head of statistical analysis, data center, and monitoring staff to define and identify cases with significant deviations from the study plan.

## **Safety analysis set (SS)**

Randomized patients administered at least one dose of the protocol treatment will be included in the SS.

# **Endpoints**

## **Primary endpoint**

Change in CAVI at 24 weeks after protocol treatment initiation as compared to that at baseline

## **Secondary endpoints**

1. Proportional change in geometric mean of urine albumin-to-creatinine ratio (UACR) at 12 and 24 weeks after the protocol treatment initiation as compared to that at baseline (important secondary endpoint)
2. Proportional change in geometric mean of blood biomarkers (pentosidine) and urinary biomarkers (type IV collagen, α1-MG, β2-MG, NGAL, NAG, L-FABP creatinine ratio) at 24 weeks after the protocol treatment initiation as compared to that at baseline

## **Other endpoints**

1. Changes from baseline in vital signs (weight, body mass index (BMI), estimated extracellular volume (eEV), blood pressure, pulse pressure, and pulse rate in the clinic, in addition to blood pressure, pulse pressure, and pulse rate at home) at 4, 12, and 24 weeks after the protocol treatment initiation
2. Changes from baseline in blood test indices (serum creatinine, estimated glomerular filtration rate (eGFR), serum cystatin C*, serum potassium, Hemoglobin A1c (HbA1c*), plasma (or serum) aldosterone concentration**, plasma (or serum) renin activity or concentration**) at 4, 12, and 24 weeks after the protocol treatment initiation (*evaluated only at baseline, and 12, and 24 weeks; **evaluated only at baseline and 24 weeks)
3. Changes from baseline in augmentation index (AI) and % mean arterial pressure at 24 weeks after the protocol treatment initiations
4. Changes from baseline in cardiac function indices (left ventricular ejection fraction (LVEF), septal e', lateral e', E, E/e'*, left ventricular mass index (LVMI), left atrial dimension (LAD), left atrial volume index (LAVI)) assessed by echocardiography 24 weeks after the protocol treatment initiation

*Three types of E/e' will be evaluated including E/septal e', E/lateral e', and E/average (septal e', lateral e')**

** average (septal e', lateral e') = (septal e' + lateral e')/2. If septal e' is missing, average (septal e', lateral e') = lateral e'. If lateral e' is missing, average (septal e', lateral e') = septal e'. If both are missing, average (septal e', lateral e') is also missing.

1. Changes in abundance of up to 181 proteins comprehensively analyzed by proteomic analysis (Olink Target 96 CVD III analysis, Olink Target 96 Inflammation analysis), 24 weeks after the protocol treatment initiation as compared to that at baseline (exploratory endpoint)

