# **Data handling**

## **Handling missing data**

Unless otherwise specified, missing values will be treated as missing values and will not be imputed with other data or used in tabulations or descriptive statistics calculations.

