## **Defining calculation items**

The change in endpoint A (participant-level) at a certain time point, t, is defined as follows:

Change in endpoint A = Endpoint A(t) - Endpoint A(baseline)

The proportional change (participant-level) of endpoint A at a certain time point, t, is defined as follows:

Proportional change of endpoint A = Endpoint A(t) / Endpoint A(baseline)

The change in the mean value of endpoint A (population-level) at a certain time point, t, is defined as follows:

Change in the mean value of endpoint A(t) = mean value of endpoint A(t) - mean value of endpoint A(baseline)

The proportional change of the geometric mean of endpoint A (population-level) at a certain time point, t, is defined as follows:

Proportional change in geometric mean of endpoint A(t) = geometric mean of endpoint A(t)/geometric mean of endpoint A(baseline)

= exp (ln (endpoint A) mean(t) - ln (endpoint A) mean(baseline))

= exp (ln (endpoint A) mean change (t))

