3. Analysis will be performed using a linear regression model with baseline values as covariates and allocation as fixed effects for each item at 24 weeks. To assess the treatment effect, the between-group difference in the change using the least squares mean at 24 weeks will be estimated using placebo group as a reference. The output will be the *P* value for testing the null hypothesis that the between-group difference in change is 0. If the distribution of values significantly deviates from a normal distribution, logarithmic values will be used for analysis as appropriate.
4. Changes from baseline in cardiac function indices (LVEF, septal e', lateral e', E, E/e'*, LVMI, LAD, LAVI) assessed by echocardiography 24 weeks after the protocol treatment initiation:
5. Descriptive statistics calculations will be conducted, and histograms will be plotted for each item and its participant-level change by treatment group and study visit. Inferential statistics calculations will be conducted for the population-level mean and its change by treatment group and study visit. If the distribution of values deviates significantly from normal distribution, the proportional change described with estimation of the geometric mean and its proportional change as appropriate.
6. Analysis will be performed using a linear regression model with baseline values as covariates and allocation as fixed effects for each item at 24 weeks. To assess the treatment effect, the between-group difference in the change using the least squares mean at 24 weeks will be estimated using the placebo group as a reference. The output will be the *P* value for testing the null hypothesis that the between-group difference in change is 0. If the distribution of values significantly deviates from a normal distribution, the logarithmic values will be used for analysis as appropriate.
7. Changes in abundance of up to 181 proteins comprehensively analyzed by proteomic analysis (Olink Target 96 CVD III analysis, Olink Target 96 Inflammation analysis) at 24 weeks after the protocol treatment initiation as compared to that at baseline (exploratory endpoint):
8. Descriptive statistics calculations will be conducted for each item and its participant-level change by treatment group and study visit. If the distribution of values deviates significantly from normal distribution, the proportional change will be described as appropriate.

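### SAP single-wall fallback for average e': if a patient's available wall differs between baseline and week 24, the change in E/average e' compares two different quantities

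*Combined protocol and SAP*

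**What the plan says.** The footnote to item 4 of Other endpoints in the SAP lists the ratios to be analysed: "Three types of E/e' will be evaluated including E/septal e', E/lateral e', and E/average (septal e', lateral e')". It defines average e' as half the sum of the septal and lateral values and then gives two fallbacks, "If septal e' is missing, average (septal e', lateral e') = lateral e'" and "If lateral e' is missing, average (septal e', lateral e') = septal e'". The average is missing only when both walls are missing.

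Three other places determine what the fallback does:

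- Defining calculation items (SAP) forms the participant-level change as "Change in endpoint A = Endpoint A(t) - Endpoint A(baseline)". It sets no condition on how the two values were obtained.
- Analysis of other endpoints (SAP) uses, for the echocardiographic indices, a "linear regression model with baseline values as covariates and allocation as fixed effects for each item at 24 weeks". No term records which wall was measured, and no analysis restricted to patients with both walls is planned.
- Handling missing data (SAP) states the general rule: "Unless otherwise specified, missing values will be treated as missing values and will not be imputed with other data".

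In the protocol, echocardiography is optional (Table 1, note 16), and an examination made before the baseline visit may serve as baseline (Scheduled observation and testing items).

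**The concern.** The SAP lists septal e' and lateral e' as separate endpoints, so it does not treat them as interchangeable. Yet the fallback lets either one stand in for their mean, separately at each visit. A patient with both walls at baseline and only the lateral wall at week 24 then has a change equal to E/lateral e' minus E/average e'. That mixes any real change with the fixed difference between the two measures.

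Mismatched walls are possible here. The examination is optional, the baseline scan may come from an earlier occasion, and the authors foresaw a single missing wall. What is at stake is the participant-level changes, histograms and mean changes by group planned for E/average e' and, under a further condition, its group comparison.

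**Working it through.** The plan states no figure on this point, so there is none to reproduce. The artefact follows from the SAP's own definitions.

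**Setup.** Hold E, septal e' (s) and lateral e' (l) constant between visits, so the true change is zero. Let r = l/s.

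- Both walls: 2E/(s + l)
- Septal alone: E/s, a relative change from both walls of (1 + r)/2 − 1
- Lateral alone: E/l, a relative change from both walls of (1 + r)/(2r) − 1
- Septal alone to lateral alone: 1/r − 1

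All are zero at r = 1 and non-zero otherwise.

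**Absolute size.** The documents give no e' values. Assume E = 70 cm/s, septal 5 to 6 and lateral 7 to 9.

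| Septal, lateral | Both walls | Septal alone (change) | Lateral alone (change) |
|---|---|---|---|
| 6, 7 | 70/6.5 = 10.77 | 11.67 (+0.90) | 10.00 (−0.77) |
| 6, 8 | 70/7 = 10.00 | 11.67 (+1.67) | 8.75 (−1.25) |
| 6, 9 | 70/7.5 = 9.33 | 11.67 (+2.33) | 7.78 (−1.56) |
| 5, 7 | 70/6 = 11.67 | 14.00 (+2.33) | 10.00 (−1.67) |
| 5, 9 | 70/7 = 10.00 | 14.00 (+4.00) | 7.78 (−2.22) |

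Over this grid the spurious change from both walls to one is about +0.9 to +4.0 (septal alone) or −0.8 to −2.2 (lateral alone).

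**Relative size over a wider assumed range of r.**

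| r | Both to septal | Both to lateral | Septal to lateral |
|---|---|---|---|
| 0.9 | −5.0% | +5.6% | +11.1% |
| 1.0 | 0% | 0% | 0% |
| 1.1 | +5.0% | −4.5% | −9.1% |
| 1.3 | +15.0% | −11.5% | −23.1% |
| 1.5 | +25.0% | −16.7% | −33.3% |

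**Group difference.** If a proportion p of an arm switches from both walls to lateral alone, the bias is roughly the difference in p between arms times the artefact per patient. At r = 1.3 and E/average e' of 10 the artefact is −1.15, so 10% against 20% gives 0.10 × −1.15 ≈ −0.12, and 5% against 25% gives 0.20 × −1.15 = −0.23.

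A simulation with no true effect agrees. It used the SAP's baseline-adjusted regression, an assumed 45 patients per arm, both walls at baseline, switching to lateral alone at week 24, r = 1.3 and 4,000 runs per setting:

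| Switching, arm 1 v arm 2 | Mean group difference | Rejection at 5% |
|---|---|---|
| 10% v 10% | about 0 | 4.8% |
| 10% v 20% | −0.12 | 6.9% |
| 5% v 25% | −0.24 | 10.4% |

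With 10% switching in each arm, the standard deviation of the estimate was 0.363, against 0.356 with no switching. That is a ratio of 1.02, within the scatter seen between settings at r = 1.0 (0.347 to 0.359). The added noise is small at that rate.

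**The case against.** The rule is explicit and prespecified, and using the available wall rather than dropping the patient is a defensible analyst's choice. A reader might infer that it contradicts the SAP's no-imputation rule. It does not, because that rule opens with an exception clause and the footnote is such an exception.

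A reader might also infer that the treatment comparison is biased. The documents do not support that. The trial is randomised and double-blind, no arm-related reason for a missing wall is evident, and equal switching left the expected group difference at zero. A difference in missingness between visits alone distorts within-group change, not the group comparison.

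The harm also needs the available walls to differ within a patient. Someone with the same single wall at both visits has no switching artefact, although the value is then not an average. How often a wall is missing is not stated, and it could be never. E/septal e' and E/lateral e' are analysed separately and are untouched, so any E/average e' result can be checked against them.

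All of this stands, and it limits the weight of the point. It does not remove the defect: where a mismatch occurs, the rule as written yields a wrong change value, and nothing in the SAP would reveal it.

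**Conclusion.** The point holds as a minor technical correction. Followed literally, the fallback gives a spurious change in E/average e' for any patient whose available walls differ between baseline and week 24, provided septal and lateral e' differ. The algebra is certain. The size rests on assumed e' values and shrinks to zero as the two walls become equal.

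If mismatches occur, within-group changes are distorted and some noise is added. Bias in the group difference needs mismatches to differ between arms in frequency or direction, and the simulated biases rest on assumed imbalances.

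The reach is narrow: one of three versions of E/e', within an endpoint classed as other, from an optional examination. It would be wrong to read this as a threat to the trial's efficacy conclusion, which the SAP bases on the primary CAVI analysis. Neither that analysis nor the sample size is involved. With the frequency of a missing wall unknown, the practical effect may be small.

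**What to change.** Amend the SAP footnote so that, for each patient, the change in E/average e' uses the same wall or walls at baseline and week 24. Use both walls where both are available at both visits, otherwise the wall common to both visits. Set the change to missing if no wall is common. Apply the same selection to the baseline covariate, and report by arm how many patients had mismatched walls. With no true change, the switching artefact is then zero for every value of r.

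The cost is a short amendment, plus the loss of patients with no common wall from this one item. A stricter rule requiring both walls at both visits would give a true average throughout but lose more patients, by a number that cannot be computed from the documents. Under either rule, single-wall data remain in the E/septal e' and E/lateral e' analyses.

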## **Safety endpoints**

Adverse events including hyperkalemia occurring after the protocol treatment initiation

# **Data handling**

## **Handling missing data**

Unless otherwise specified, missing values will be treated as missing values and will not be imputed with other data or used in tabulations or descriptive statistics calculations.

## **Handling of data at the time of discontinuation**

In safety analysis, data at the time of discontinuation will be treated as data from the most recent measurement after a specified study visit before the discontinuation. If a measurement at the time of discontinuation is conducted after the last study visit specified, it will not be included in the descriptive statistics compilation or calculation.

## **Defining calculation items**

The change in endpoint A (participant-level) at a certain time point, t, is defined as follows:

Change in endpoint A = Endpoint A(t) - Endpoint A(baseline)

The proportional change (participant-level) of endpoint A at a certain time point, t, is defined as follows:

Proportional change of endpoint A = Endpoint A(t) / Endpoint A(baseline)

The change in the mean value of endpoint A (population-level) at a certain time point, t, is defined as follows:

Change in the mean value of endpoint A(t) = mean value of endpoint A(t) - mean value of endpoint A(baseline)

The proportional change of the geometric mean of endpoint A (population-level) at a certain time point, t, is defined as follows:

Proportional change in geometric mean of endpoint A(t) = geometric mean of endpoint A(t)/geometric mean of endpoint A(baseline)

= exp (ln (endpoint A) mean(t) - ln (endpoint A) mean(baseline))

= exp (ln (endpoint A) mean change (t))

# **Output statistics and significance levels for hypothesis tests**

## **Descriptive statistics**

The outputs will be number of cases, mean, standard deviation, minimum, 25th percentile, median, 75th percentile, and maximum and number of missing values.

